### Data analysis

Data will be generated from the on-line data management system and analysed in SPSS. The primary analysis will be based on all subjects with outcome data available. Any participants with protocol violations, including women who no longer wish to receive their allocated intervention but are prepared to have data collected, will be analysed in the group to which they were allocated (intention-to-treat). Data from subjects who withdraw their consent will be excluded from the analysis and considered as lost to follow-up.

Baseline characteristics will be compared between groups to confirm the effectiveness of the randomization process in creating similar groups. Numbers and baseline characteristics of women lost to follow-up will also be compared between study groups to detect any imbalances.

Most study outcomes are categorical variables. For these types of variables, the number of subjects, number of missing values and percentages will be reported. Categorical variables will be compared between study arms as risk ratios with 95 % confidence intervals.

For continuous variables, e.g. time to delivery, the number of subjects, and number of missing values, minimum, maximum, means and standard deviations will be reported. Appropriate transformation of non-normal or skewed measurement will be performed. Means will be compared using t-tests for two independent samples, and 95 % confidence intervals will be calculated. If transformations do not generate a distribution approaching normality, medians and interquartile range (IQR) will be reported. The primary outcome of the study is “mean time (minutes) from randomization to delivery”. The survival technique log-rank test will also be used to compare the survival rates of the three groups, pairwise. Results will be reported according to CONSORT guidelines [22].

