## Methods

### Study design

The GAP study is a multicentre, randomized, controlled, unblinded, clinical trial with three parallel arms (1:1:1). Please see Fig. 1 for a graphical outline of the study.

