### Safety considerations

No drugs are being tested in this study. We are testing interventions that are not taught or sanctioned by teaching institutions in South Africa or elsewhere due to lack of evidence, but practiced to varying degrees of frequency. WHO does not currently recommend this procedure. The GAP method of applying fundal pressure has been specifically developed to avoid the commonly used, more vigorous form of fundal pressure. Therefore, interventions which are practiced to some extent (fundal pressure and posture) but for which there is little supporting evidence are being tested by the study. We do not anticipate any specific safety concerns over and above those usually anticipated in the second stage of labour.

However, some women may find specific birth positions and/or gentle fundal pressure uncomfortable. The research staff will assist and support women to use the allocated study position. Women may benefit from the additional support. However, should a woman choose to change birth position, or withdraw from the study for any reason, it will not affect the medical care to which she is entitled.

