### Criteria for discontinuation

Criteria for discontinuation of a participant

Participants who no longer wish to remain in the study will be discontinued.

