### Follow-up procedures

Delivery details of screened, consenting women who are not enrolled/randomized (e.g. who deliver before enrolment by caesarean section or vaginal delivery) will be recorded on the relevant screening form.

Participating women and their neonates must be followed up until discharge from the maternity and neonatal units. Therefore, we do not anticipate any loss to follow-up. The case report forms are available upon request.

For quality control, in a subset of cases a mobile phone or camera-based video and sound recorder with recorded time display may be set up behind the woman prior to random allocation. The recorder will be positioned so that the mother’s identity is not seen. The researcher’s recorded voice must document the time at which the randomization envelope is opened, the posture of the woman, the use of fundal pressure, and the time of delivery of the baby. The times will be transcribed from the time sheet and/or the recording to the paper CRF.

Recordings will only be used for research purposes; to assess quality of recording of timing of events. These recordings will be kept securely with other trial documentation in the research office and be accessible only to research staff. At the end of the study all recordings will be destroyed.

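### The consent-withdrawal rule discards data already collected from randomized women and so departs from intention-to-treat; bias is possible, but its direction and size are unknown

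*Protocol article*

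**What the plan says.** Four statements in the Data analysis section of the protocol article bear on this.

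- The analysis set is available-case: "The primary analysis will be based on all subjects with outcome data available".
- Protocol violators are covered by a rule that the article labels intention-to-treat: "including women who no longer wish to receive their allocated intervention but are prepared to have data collected, will be analysed in the group" (that is, the randomized arm).
- For full withdrawal the rule differs: "Data from subjects who withdraw their consent will be excluded from the analysis and considered as lost to follow-up".
- One check is planned: "Numbers and baseline characteristics of women lost to follow-up will also be compared between study groups to detect any imbalances".

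Elsewhere, Study design describes the trial as unblinded with three arms. Criteria for discontinuation says: "Participants who no longer wish to remain in the study will be discontinued". Safety considerations notes that "some women may find specific birth positions and/or gentle fundal pressure uncomfortable", and treats changing position and leaving the study as separate choices. Ethical considerations lets a woman withdraw at any point after signing consent. Follow-up procedures follows mother and baby until discharge and concludes: "Therefore, we do not anticipate any loss to follow-up".

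**The concern.** The exclusion has no time limit. It covers information validly collected before the woman changed her mind, not only what would have been collected afterwards. Follow-up runs to discharge, so a woman may withdraw after delivery, when her primary outcome and some of her baby's outcomes are already recorded. The rule then deletes known results from a randomized participant.

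Withdrawal happens after allocation, and everyone knows the arm. It may be related to the arm, to how long labour is lasting, or to how the birth went. An analysis that drops such women no longer compares the groups as randomized. At stake are the comparison of mean times and the final comparison of neonatal and maternal harms. The article itself says that the safety of fundal pressure has not been established, so losing even a few adverse outcomes would matter.

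**Working it through.** **Inputs.** From Statistical methods: target difference 3 min; control mean 23.1 min, SD 12.2; fundal-pressure mean 18.6 min, SD 9.5; nominal alpha about 0.02 per comparison; 347 per arm, raised to 382. The article gives no withdrawal rate and no times for women who withdraw, so both are assumed below.

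**The plan's own figure.** With n = 2(z_alpha/2 + z_power)² SD²/3² and 90% power, SD 10.93 (root mean of the two variances) and alpha 0.02 give 346; SD 12.2 and alpha 0.05 give 348. Either is close to 347. Then 347 × 1.10 = 381.7, hence 382. That 10% is for non-compliance, not withdrawal. The present point does not depend on how 347 was reached.

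**Whom the rule reaches.**

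1. A woman stops the posture or pressure but allows data collection: kept in her arm. No loss.
2. A woman withdraws consent while undelivered: she has no delivery time yet, so the rule deletes no primary value. It does delete the known fact that she was undelivered up to that time, which the log-rank analysis could use. Her delivery time can be recovered only with permission to read the hospital record.
3. A woman withdraws consent after delivery and before discharge: a recorded delivery time, and possibly neonatal outcomes, are deleted.

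**Size.** Let w be the share of an arm excluded, and D the minutes by which the excluded women exceed the retained women on average.

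Full-arm mean − retained mean = w × D

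The between-arm bias is the difference in w × D between the two arms. If only one arm loses women, it is w × D.

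For type I error, with SD 12.2 in both arms and alpha 0.02 two-sided: SE = 12.2 × √(1/382 + 1/[382(1 − w)]), and error = Φ(b/SE − 2.326) + Φ(−b/SE − 2.326), where b = w × D. Example, w = 5% and D = 20: b = 1.0, SE = 0.894, b/SE = 1.118, error = 0.114.

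| w (one arm) | Women of 382 | Bias, D = 10 to 20 min | Share of 3 min | Type I error (nominal 0.02) |
|---|---|---|---|---|
| 1% | about 4 | 0.1 to 0.2 min | 3 to 7% | 0.021 to 0.023 |
| 2% | about 8 | 0.2 to 0.4 min | 7 to 13% | 0.023 to 0.033 |
| 5% | about 19 | 0.5 to 1.0 min | 17 to 33% | 0.041 to 0.114 |
| 10% | about 38 | 1.0 to 2.0 min | 33 to 67% | 0.111 to 0.452 |

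**Is D of 10 to 20 min plausible?** Assume gamma-distributed times with mean 23.1 and SD 12.2. Excluding a random 3% of the arm from women above 20 or 30 min lowers its mean by 0.26 or 0.53 min; excluding 5% lowers it by 0.45 or 0.89 min. Dividing by w gives D of about 9 min (0.26/0.03 = 8.7; 0.45/0.05 = 9.0) and about 18 min (0.53/0.03 = 17.7; 0.89/0.05 = 17.8). The assumed range is therefore reasonable if withdrawals come from long labours, which is itself an assumption.

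**Limits.** A spurious 3 min would need D = 3/0.05 = 60 min at 5%, or 3/0.10 = 30 min at 10%. If w × D is equal in two arms, the bias between them cancels. If excluded women had shorter times, D is negative and the bias reverses.

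**The case against.** The strongest reply is that the article already has a two-tier rule. A woman who dislikes kneeling or pressure can stop and still be analysed as allocated, so discomfort leads first to non-compliance, not exclusion. Only full withdrawal triggers the rule; the article expects no loss, and mean times of roughly 19 to 23 min leave little opportunity to withdraw before delivery. All of this stands, and it makes a low exclusion rate likely. It does not justify discarding data already collected from those who do withdraw.

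A reader might go further and infer that the rule tilts the result toward the two upright arms, because discomfort there would drive out the slowest labours. The documents do not support that. Safety considerations says only that some women may be uncomfortable, and adds that they may benefit from the extra support. Withdrawal is not confined to labour, so it need not select slow ones. Women in routine care may withdraw too. Nothing gives withdrawal by arm or the times of those who leave.

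Two further replies also stand. Comparing the numbers lost between arms is already planned, and the unseen statistical analysis plan may hold sensitivity analyses, so neither is counted as missing. The planned baseline comparison can, however, reveal an imbalance but not correct outcome-related exclusion. Adverse events also go to the data safety and monitoring committee separately, so safety oversight during the trial does not rest on this analysis set; the final comparison does.

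**Conclusion.** The point holds as a fault in a stated rule, not as a demonstrated bias. Deleting all data from women who withdraw consent, including data collected beforehand, is inconsistent with the intention-to-treat comparison the same paragraph names. The article expects delivery and discharge in hospital, so much of the resulting missing data would be avoidable.

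The likely effect on the primary mean is small: at most 0.4 min at 1 to 2% exclusion, assuming one arm only and an excess of up to 20 min. It becomes material at about 5% (0.5 to 1.0 min), a rate the documents give no reason to expect. The direction is unknown. The case for change rests mainly on the rule being worse than an easy alternative, and on rare harms that deletion could remove from the final comparison.

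**What to change.** Replace the withdrawal sentence in Data analysis with a rule of three parts:

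1. Data collected up to withdrawal stay in the allocated arm. A woman undelivered at that moment contributes a time censored at withdrawal to the log-rank analysis.
2. At withdrawal she is asked whether delivery time and newborn outcome may be taken from the hospital record. This is the part that protects the mean for women who leave before delivery, since a censored time does not enter a t-test.
3. Only data whose use she refuses are excluded.

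The cost is ethics committee agreement to the wording and one line on the withdrawal form. Sample size and the main analysis method do not change.

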### Study setting

The study will be conducted in four sites at three maternity facilities in South Africa, namely:Frere Hospital, East London – a tertiary-level hospital with approximately 800 beds in total, with an estimated 570 deliveries per month. There are two study sites at Frere Hospital:oDancan Village Day Hospital - Midwife-led obstetric unitoFrere labour ward - Obstetrician-led obstetric unitCecilia Makiwane Hospital, East London – a secondary-level hospital with approximately 700 beds in total, with an estimated 400 deliveries per monthButterworth Hospital – a district hospital with approximately 400 beds in total, with an estimated 400 deliveries per month

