### Sampling and allocation

Recruited women who reach second stage of labour without major complications will be randomized. The randomization sequence will be generated by the WHO/RHR Statistics and Informatics (SIS) team. This will be computer-generated in balanced blocks of variable size, in a ratio of 1:1:1 for the three study arms. Details of the group allocation will be concealed on cards inside a sequentially-numbered series of sealed, opaque envelopes. These will be prepared by the SIS team, separately for each study site. Allocation will be performed by the research assistant, by opening the next numbered envelope in the series. The assignment schedule will be stored at WHO, and will not be accessible to the on-site research teams.

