#### Arm 3: Routine practice (recumbent/supine posture only)

The current posture as practiced in the participating sites will be used.

In all intervention arms, the trained birth attendant encourages the women to bear down. All other delivery procedures, such as fetal heart monitoring and routine oxytocin after the birth, are performed according to the usual hospital routine and will not differ between the groups.

For Arm 3 (routine practice), if the woman remains undelivered 30 min after randomization, fundal pressure or changes in posture may be considered necessary by the birth attendant according to routine local practice. Additional procedures or treatments performed at the discretion of the attendant will then be recorded in the study form.

At any stage of the labour, routine procedures such as change in posture, oxytocin administration, forceps or vacuum delivery or caesarean section will be available as considered indicated by the responsible clinician. If forceps, vacuum delivery or caesarean section is required, GAP and/or upright only posture will be stopped.

Electronic fetal heart rate monitoring is not routinely used in the study institutions in uncomplicated pregnancies; therefore, this equipment is unlikely to interfere with the administration of the interventions in this study. Auscultation of the fetal heart rate will be performed after each contraction following randomization. If electronic monitoring is considered necessary by the birth attendant, the GAP procedure will not interfere with monitoring as the monitor is positioned on the anterior aspect of the uterus while pressure is applied to the fundal aspect.

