### Study outcomes

The primary outcome is defined as mean time (minutes) from randomization to delivery.

Secondary outcomes include the following:Delivery outcomes:oNo spontaneous delivery within 15 min of randomization;oOperative delivery (vacuum, forceps or caesarean section); andoEpisiotomy or 2nd/3rd degree tears.Neonatal outcomes: oCord blood pH < 7.2;o5-min Apgar score <7;oNeonatal injury;oNeonatal encephalopathy;oAdmission to neonatal high care nursery for ≥24 h; andoNeonatal death.

Mothers will also be asked to grade their discomfort experienced during the second stage of labour. All adverse events and serious adverse events will also be recorded.

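### Allocation is blocked separately by site, but the stated comparisons leave site out, so standard errors are somewhat too large if sites differ

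*Protocol article*

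**What the plan says.** Under Sampling and allocation, the sequence is "computer-generated in balanced blocks of variable size, in a ratio of 1:1:1 for the three study arms". Of the sealed envelopes the section says: "These will be prepared by the SIS team, separately for each study site". Under Study setting, "The study will be conducted in four sites at three maternity facilities in South Africa". These are a midwife-led unit and an obstetrician-led labour ward, both under the tertiary hospital, a secondary-level hospital, and "a district hospital with approximately 400 beds in total". The control arm follows local habit: "The current posture as practiced in the participating sites will be used".

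On outcomes, "The primary outcome is defined as mean time (minutes) from randomization to delivery". For the analysis, "Means will be compared using t-tests for two independent samples", and "Categorical variables will be compared between study arms as risk ratios with 95 % confidence intervals". The Data analysis section also names a pairwise log-rank test. Site appears in none of these comparisons, and no site adjustment is mentioned elsewhere in the article.

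**The concern.** Separate blocked series per site hold the arms in nearly equal proportions within each site. A difference in average delivery time between sites therefore almost cancels out of the difference between arms. A plain two-sample t-test does not know this. It estimates the error variance from the whole spread within each arm, including the part that lies between sites. The same holds for a crude risk ratio interval and an unstratified log-rank test.

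Sites plausibly differ. They work at different levels of care, and both the control posture and the use of additional procedures follow local practice. If so, intervals are wider and p-values larger than the design warrants, and some of the precision that the randomization bought is not used.

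**Working it through.** **Inputs.** From Statistical methods: difference 3 min, SDs 12.2 and 9.5 min, alpha 0.05/3 rounded to 0.02, power 90%, 347 women per arm before the non-compliance allowance. The article does not say whether the test is one- or two-sided; two-sided is used here. The share *f* of the variance in time that lies between sites is not given. I take 2%, 5% and 10% as an assumed range, equal in both arms.

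**The plan's own figure.** Average variance = (12.2² + 9.5²)/2 = (148.84 + 90.25)/2 = 119.545, so SD = 10.93. Then n = 2 × 119.545 × (2.326 + 1.282)²/3² ≈ 346 per arm by the normal approximation, and 347.2 with the t distribution. The stated 347 is reproduced, and power at 347 is 90.0%. An SD of 12.2 with alpha 0.05 also comes close (348 per arm), so the article does not settle which inputs were used. The power figures below belong to the first set; the standard-error ratios and test sizes do not depend on the SD.

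**Standard errors.** The plain t-test uses SE = 10.93 × √(2/347) = 0.830 min. With arms balanced within site, the true SE of the difference is 0.830 × √(1−f). The reported SE is therefore too large by the factor 1/√(1−f).

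**Test size and coverage.** The true size of the nominal 0.02 test is 2 × [1 − Φ(2.326/√(1−f))]. The true coverage of the nominal 95% interval is 2 × Φ(1.96/√(1−f)) − 1.

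**Power.** Both analyses have noncentrality 3/(true SE), on 692 degrees of freedom. The adjusted test uses the critical value 2.332. The unadjusted test in effect uses 2.332/√(1−f).

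| Assumed f | True SE (min) | Reported SE too large by | True size of 0.02 test | Coverage of 95% CI | Power, unadjusted | Power, adjusted |
|---|---|---|---|---|---|---|
| 0 | 0.830 | 0% | 0.0200 | 95.0% | 90.0% | 90.0% |
| 2% | 0.822 | 1.0% | 0.0188 | 95.2% | 90.2% | 90.6% |
| 5% | 0.809 | 2.6% | 0.0170 | 95.6% | 90.6% | 91.5% |
| 10% | 0.787 | 5.4% | 0.0142 | 96.1% | 91.1% | 93.0% |

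Like for like, before rounding, adjustment gains about 0.4, 1.0 and 1.9 percentage points of power.

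**Check by simulation.** With four equal sites, SD 12.2 and f = 10%, 20,000 trials without an arm effect gave a rejection rate of 1.4% for the unadjusted test and 1.9% for the site-adjusted test, at nominal 2%. The unadjusted 95% interval covered about 96%. This agrees with the formulas.

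**The case against.** The strongest reply is that the effect may be close to nil. Entry is limited to nulliparous women with a singleton cephalic pregnancy and no chronic conditions or obstetric complications, and the clock starts only at randomization, after 15 to 30 min of second stage. Both narrow the case mix. The sites differ in level of care, which does not show that they differ in delivery time. This stands: the omission is certain from the text, but its size is not.

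A second reply is that stratum adjustment is often left to the analysis plan, which the article says is finalised before recruitment and which is not at hand. That plan may already include site. The reply has limited force, because the article does not leave the method open: it names the tests, and as written they do not match the randomization.

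Three stronger readings are tempting, and the documents do not support them:

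- **That the results would be invalid.** The error runs only in the conservative direction, the effect estimate is unbiased, and the sample size stands.
- **That adjustment is needed to rescue a shortfall in power.** On the inputs used here, the stated 90% is met at 347 per arm without it.
- **That the gain is the adjusted power minus 90.0%**, that is 0.6, 1.5 or 3.0 points. The 90.0% holds only if site explains nothing. Where site matters, blocking also makes the unadjusted difference less variable, so unadjusted power rises too.

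**Conclusion.** The point holds as a matter of efficiency and of matching the analysis to the design. The named analyses ignore the factor by which women are randomized. The consequence is conservative inference of modest size: a standard error 1.0% to 5.4% too large and about 0.4 to 1.9 points of power forgone, if site explains 2% to 10% of the variance in time. This rests on an assumed range for that share, on near balance of arms within site, and on two-sided testing at 0.02 with SDs 12.2 and 9.5. If sites do not differ in outcome, there is no loss. It is worth correcting because the remedy is simple.

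**What to change.** - **Primary outcome:** analyse minutes from randomization to delivery with a linear model on arm and site (four levels), using robust standard errors, and report the site-adjusted mean difference for each pair of arms.
- **Log-rank test:** stratify each pairwise test by site.
- **Categorical outcomes:** report Mantel-Haenszel risk ratios stratified by site where event counts allow. For very rare events, such as neonatal death, keep crude or exact methods.

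The four strata should be the sites for which the envelope series were prepared, not the three hospitals. If the analysis plan already does this, the protocol text only needs to be brought into line. The cost is a change of wording: site is already recorded, and neither the sample size nor the conduct of the trial changes. The wording should be settled before any comparison between arms is seen, including the planned interim analysis.

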### Statistical methods

The sample size has been calculated to be powered to detect a reduction in the primary outcome of mean time (minutes) from randomization to delivery of > =3 min. A reduction of > =3 min was used due to the findings of the study by Api et al (2009) [31], that reported a time from randomization to delivery of 23.1 min (SD 12.2 min) in the control group (*N* = 56), and 18.6 min (SD 9.5 min) in the fundal pressure group (*N* = 34). We assumed that upright posture alone would likely lie between these two (i.e. approximately 20.0 min). Using the Bonferroni rule to control for multiplicity, alpha is divided by the number of comparisons (0.05/3 ≈ 0.02). We assumed a power of 90 % and alpha of 95 %. The study therefore requires 347 women in each arm, i.e. 1,041 women for all three arms. To allow for 10 % non-compliance, we aim to recruit 382 in each arm. The final sample size for the whole study is 1,145 women.

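### The design applies a Bonferroni correction to the three primary comparisons, but the analysis section reports them with unadjusted 95% intervals and does not carry the adjusted level forward

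*Protocol article*

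**What the plan says.** The Study objectives section of the protocol article lists three comparisons and ranks none above the others: GAP against routine practice, upright posture against routine practice, and GAP against upright posture. The Study outcomes section sets the endpoint: "The primary outcome is defined as mean time (minutes) from randomization to delivery".

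The Statistical methods section sizes the trial with a multiplicity rule: "Using the Bonferroni rule to control for multiplicity, alpha is divided by the number of comparisons (0.05/3 ≈ 0.02"). The next sentence gives 90% power and describes alpha as 95%, which is evidently a slip and leaves the working level less clear than it should be.

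The Data analysis section is the only place that says how means are compared: "Means will be compared using t-tests for two independent samples, and 95 % confidence intervals will be calculated". The sentence covers continuous variables in general, but time to delivery is the example given, and nearly all the listed secondary outcomes are categorical. The section also plans pairwise log-rank tests. It gives no significance level for either kind of test, and it does not mention the Bonferroni level again.

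**The concern.** A 95% interval excludes zero exactly when a two-sided 5% test rejects. A design that spends 0.05/3 on each comparison and a report that shows 95% intervals therefore use two different yardsticks for the same three differences. One comparison can have an interval that excludes zero and a p value that fails the Bonferroni threshold, and the article does not say which decides.

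This matters because the Discussion ties practice to the result: promote the gentle method if it helps, discourage fundal pressure if it does not. The comparison that isolates the pressure itself, GAP against upright posture, has the smallest assumed difference and is the most likely to land where the two yardsticks disagree. Without a stated rule, that choice could be made after the results are seen.

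**Working it through.** **Inputs, all from Statistical methods.** Target difference 3 min; SD 12.2 min (control) and 9.5 min (fundal pressure); power 90%; 347 women per arm; three comparisons; assumed means 23.1 (routine), about 20.0 (upright) and 18.6 (GAP). Two-sided testing is my assumption, since the article does not state sidedness.

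**1. Reproduce the sample size.** n per arm = 2·SD²·(z₁₋α/₂ + z₀.₉₀)²/δ².
- Average variance (12.2² + 9.5²)/2 = 119.5, so SD = 10.93.
- α = 0.02: 2 × 119.5 × (2.326 + 1.282)²/9 = 346, against 347 stated.
- α = 0.05/3: 2 × 119.5 × (2.394 + 1.282)²/9 = 359.
- α = 0.05 with SD 12.2 in both arms: 2 × 148.8 × (1.960 + 1.282)²/9 = 348.

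The stated figure fits the rounded Bonferroni level. It also fits an unadjusted 5% level with the larger SD, so the sample size alone does not prove which level was meant.

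**2. Family-wise error with all arms equal.** For three equal arms, the chance that at least one pairwise |z| exceeds a critical value z is P(Q > z√2), where Q is the studentized range of three means.

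| Interval | z | z√2 | Chance of at least one false difference |
|---|---|---|---|
| 95% | 1.960 | 2.772 | 12.2% |
| 98% (rounded 0.02) | 2.326 | 3.290 | 5.2% |
| 98.33% (0.05/3) | 2.394 | 3.386 | 4.4% |

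The t version with 347 per arm and a simulation of 1,000,000 trials agree to within rounding. The independence formula, 1 − 0.95³ = 14.3%, overstates the first figure because the three differences share arms.

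**3. Width of the intervals.** SE = 10.93 × √(2/347) = 0.830 min.
- 95%: 1.960 × 0.830 = 1.63 min.
- 98%: 2.326 × 0.830 = 1.93 min.
- 98.33%: 2.394 × 0.830 = 1.99 min.
- Ratio 2.394/1.960 = 1.22, so 22% wider.

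An observed difference between 1.63 and 1.93 min (at 0.02) or 1.99 min (at 0.0167) excludes zero on the 95% interval and fails the adjusted test.

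**4. How often that happens.** P = Φ((upper − δ)/SE) − Φ((1.63 − δ)/SE), with unrounded limits.

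| True difference δ | Upper limit 1.93 | Upper limit 1.99 |
|---|---|---|
| 1.4 min (20.0 − 18.6, GAP against upright) | Φ(0.64) − Φ(0.27) = 13% | Φ(0.71) − Φ(0.27) = 15% |
| 3 min (design target) | Φ(−1.29) − Φ(−1.65) = 5% | Φ(−1.22) − Φ(−1.65) = 6% |
| 4.5 min (23.1 − 18.6, GAP against routine) | about 0.1% | about 0.1% |

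The assumed gap between upright posture and routine practice, 23.1 − 20.0 = 3.1 min, lies close to the second row.

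**The case against.** A reader might infer that the trial runs a 12% risk of a false primary claim in place of the intended 5%. The article does not support that. It compares means by t-tests and says intervals will be calculated. It does not say that claims are read from the intervals, and it does not set the tests at 5%. The only testing rule in the document is the Bonferroni one. Read together, the two sections most naturally mean t-tests judged at about 0.02, which gives 5.2%. This objection stands, and it limits the point to a mismatch between interval and test.

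Other points on that side also carry weight:
- An unadjusted 95% interval is a valid estimate for a single comparison, and showing it beside adjusted tests is defensible. The three 95% intervals cover all true differences together about 88% of the time (100 − 12.2), but the article never promises joint coverage.
- The 12.2% counts false differences in either direction. The objectives speak of reduced duration. Counting one fixed direction per pair, the figure is 6.6%, against 2.3% to 2.8% at the adjusted levels.
- For GAP against routine practice, conflict is very unlikely at the assumed gap.

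A further argument is that the interval level belongs in the statistical analysis plan, which is to be finalised before recruitment and is not shown here. That weakens the point but does not remove it: the article does not leave the level open, it prints 95%, and time to delivery is its named example.

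**Conclusion.** The mismatch is real. The interval level printed for the primary comparisons does not follow the design's own multiplicity rule, and nothing says whether the interval or the adjusted test decides.

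Its size depends on how claims are made. If they are read from the 95% intervals or from 5% tests, the two-sided family-wise error is about 12%, against 4.4% to 5.2%. If the tests use the Bonferroni level, error is controlled roughly as designed and the harm is confined to contradictory reporting in a band of about 0.3 to 0.4 min, mainly for GAP against upright posture.

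These figures assume two-sided tests, equal arms of 347, a common SD of 10.93 min and approximately normal mean differences on the minutes scale. A different SD or a transformation would move the band but not the family-wise rates. The point should be fixed; it does not call the design, the outcome or the choice of test into question.

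**What to change.** In Data analysis, state that the three primary mean differences are each tested two-sided at 0.05/3 = 0.0167 and reported with matching 98.33% intervals. Label any unadjusted 95% interval for the primary outcome as descriptive and not used for the claim. The 95% intervals for secondary outcomes can stay. In Statistical methods, correct the sentence that describes alpha as 95%, so that one level runs through both sections.

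The cost is a few words and primary intervals about 22% wider (half-width 1.99 against 1.63 min at 347 per arm). Using the exact 0.0167 in place of the rounded 0.02 lowers power at 3 min from 90.1% to 88.9% with 347 per arm and SD 10.93. No further data are needed.
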